## Abstract

**Background:**

Smoking is the leading risk factor for postoperative complications and is associated with longer hospital stays, reoperations, and 30-day mortality. Smoking rates among patients undergoing major elective surgery are high (22.3%‐43.0%). It is urgent to identify efficacious, strategically timed smoking cessation interventions for patients undergoing surgery.

**Objective:**

The goal of this pilot randomized controlled trial is to design and test the feasibility of the first mobile contingency management (mCM) smoking-cessation intervention for military veterans undergoing major elective surgery and to evaluate the effectiveness of mCM compared to treatment as usual (TAU) as exploratory analysis.

**Methods:**

We will adapt and adjust a contingency management protocol for delivery over 5 weeks using mobile carbon monoxide monitoring in the perioperative period. We will then test its feasibility and effectiveness in veteran smokers undergoing major elective surgery (n=36). Participants will be randomized to receive mCM or TAU. Both groups will receive pharmacotherapy. The feasibility of mCM will be assessed by (1) recruitment rate, (2) level of engagement, and (3) retention. We will also compare mCM with TAU on smoking cessation outcomes (quit attempts, cigarettes per day, and nicotine dependence severity) over 5 weeks to examine effectiveness.

**Results:**

This pilot trial has been funded since July 2024, and a 1-year no-cost extension has been granted through June 2027. The recruitment and data collection started in December 2025. The first participant consented on December 12, 2026. As of May 2026, 18 participants have been enrolled and randomized in this pilot trial. Enrollment of the last participant is expected to be in March 2027 to reach a target of 36 enrolled participants, and the data collection is expected to be completed by April 2027. There will be no interim data analysis, but preliminary analysis is expected to be completed by August 2027, and all data analyses will be completed by the end of 2027.

**Conclusions:**

Novel interventions to support smoking cessation may reduce morbidity, mortality, and health care costs for patients undergoing major surgery. mCM has a high potential to implement widely to improve surgical outcomes.

## Introduction

### Background

Major surgery is common among veterans, and smoking is the most significant modifiable risk factor for perioperative morbidity and mortality [1]. The Veterans Affairs (VA) Health Care System performs over 600,000 major elective surgeries annually, including general, thoracic, vascular, urologic, spinal, and other orthopedic procedures [2]. Unfortunately, smoking prevalence among patients undergoing major elective surgery is high, ranging between 22.3% and 43.0%, and is highest among uninsured patients (36.3%) and Medicaid recipients (43.0%) [3]. Reducing complications and death after major elective surgery is a top priority for both veterans [1] and the general population [3]. Smoking-related postoperative risks include pneumonia, prolonged intubation, myocardial infarction, and stroke [4-6]; infections, sepsis, and poor wound healing [4-9]; and repeat procedures [4-9]. Active smoking status at the time of surgery is the single greatest risk factor for complications, reoperation, and death [4-9]. The relative risk (RR) of death in 30 days following major surgery is 1.5 times higher in smokers than in nonsmokers [8,9]. Accordingly, the American College of Surgeons recommends that smoking cessation counseling be offered during all nonemergent consultations [9].

The preoperative period offers a critical opportunity to promote behavior change [3,10,11]. A systematic review of clinical trials found that intensive perioperative smoking cessation programs, with sessions before and after surgery, increased the likelihood of postoperative abstinence in both the short term (odds ratio 2.41, 95% CI 1.95-2.98) and the long term (odds ratio 1.64, 95% CI 1.23-2.20) [10]. Another systematic review and meta-analysis examining rehabilitation interventions for behavioral change concluded that participation in 4-week behavioral interventions before surgery was associated with higher odds of cessation (RR 2.9, 95% CI 1.7-4.8; *I*^2^=84%) and sustained abstinence at 12 months post surgery (RR 1.74, 95% CI 1.20-2.55; *I*^2^=43%) [11]. Taken together, intensive smoking cessation interventions before and after surgery can improve short-term and long-term quit rates.

Contingency management (CM) is a behavioral treatment that uses positive reinforcement to incentivize behavior change through financial rewards (ie, vouchers and cash equivalent) when the target behavior (eg, smoking cessation) is achieved and biologically verified. CM interventions are associated with rapid reductions in substance use during the active delivery of incentives [12,13] and are effective for a range of substance use disorders (SUDs), including tobacco use disorder (TUD) [14-18], in both men and women [19]. A Cochrane review examining CM for smoking abstinence compared with controls reported a pooled risk ratio of 1.49 at the longest follow‐up (6 mo or more) [20]. CM is commonly combined with other evidence-based treatments for TUD such as pharmacotherapy and behavioral counseling [21] and can be strategically timed to promote abstinence at a crucial period when the clinical benefit of cessation is substantial. The VA is a leader in implementing CM for a range of SUD [22,23], delivering CM to over 7700 veterans across 134 sites since 2011. While CM for stimulant use disorder is well established in the VA, CM for smoking cessation is in the earlier stages of implementation.

A fixed-incentive CM structure is flexible and suited to remote delivery, while the optimal frequency, timing, and duration of financial incentives to promote durable, long-term abstinence are areas of active inquiry [24]. CM incorporates clinician feedback at the time of bioverification and incentive; feedback is brief, focused on the target behavior, and includes praise for abstinence, expressions of empathy and confidence, assessment of the target behavior and craving, and encouragement of follow-up [25].

Attendance and retention are key predictors of CM outcomes; thus, CM protocols for smoking cessation must include replicable, consistent bioverification [20,25-28]. Advances in digital health have facilitated remote CM bioverification and monitoring of smoking abstinence using a personal, mobile carbon monoxide (CO) device at home. A recent meta-analysis concluded that CM delivered via telehealth is an efficacious intervention for SUD, including TUD [14] (pooled effect sizes for the percentage of negative samples [*d*=0.94], longest duration of abstinence [*d*=1.08], and quit rate [*d*=0.46]). In clinical research, mobile contingency management (mCM) for smoking cessation with CO bioverification has shown benefits in different veteran populations [14,20], including those in rural areas [29], those who are unhoused [27], and those with SUD [30] and posttraumatic stress disorder [31]. CM is safe; problem gambling is the only relative contraindication to CM, due to the potential to reactivate gambling behaviors [32]. CM has numerous advantages for veterans undergoing major surgery, given its association with rapid reduction in tobacco use, its ability to be strategically timed for the highest impact, its excellent safety profile with few contraindications, and its scalability within the VA system. CM for TUD delivered perioperatively may prolong lifespan, reduce complications, cut health care expenditures, and enhance quality of life.

To our knowledge, only 1 randomized controlled trial (RCT) [33] has tested CM for smoking in the perioperative setting; CM predicted more rapid abstinence, a lower percentage of positive tests, and fewer lapses following abstinence [33]. However, gaps exist in terms of feasibility and methodological considerations, given that this CM protocol in the aforementioned RCT did not employ bioverification 5 to 7 days per week to verify abstinence and was conducted in a surgical cohort with cancer. No trials that we are aware of have examined CM for a broader population of patients undergoing major elective surgery, delivered remotely, or examined a more rigorous CM schedule to bioverify abstinence.

The present proof-of-principle pilot study addresses a critical gap in perioperative care by providing a scalable, digital CM solution that meets the specific needs of veterans and other high-priority groups. Although CM for TUD has strong empirical evidence, it has never been trialed before and after major surgery nor tested in a VA context. Moreover, no smoking-cessation RCT of CM with near-daily mobile bioverification—now considered a first-line approach [26,27]—has been conducted with patients undergoing major elective surgery. Research indicated that behavioral interventions for smoking cessation before surgery [11] and continuation after surgery [10] are associated with favorable outcomes [24]. This investigation aims to establish mCM as an effective approach for perioperative smoking cessation, with the potential to inform broader CM applications.

### Study Objectives and Aims

In this pilot RCT, veteran smokers undergoing major elective surgery (n=36) will be randomized to receive the 5-week mCM protocol or 5 weeks of treatment as usual (TAU; offering VA Tobacco Cessation Clinic and VA Telephone Quitline) remotely. The mCM smoking-cessation protocol will comprise a 5-week, fixed-incentive schedule, including once-daily CM incentives contingent on bioverified abstinence, weekly behavioral coaching, and remote CO monitoring. Both groups will be offered smoking-cessation medication [21]. Our first aim (aim 1) is to develop an mCM smoking-cessation protocol to be integrated into VA surgical settings. This protocol will modify an extant CM model for smoking cessation within the VA [34] to be adapted for delivery via telehealth. Additional aims include assessing the feasibility of CM for TUD in surgical settings (aim 2) and comparing CM with TAU (exploratory aim). We predict that CM will be feasible in the surgical setting, as assessed by measures of enrollment, retention, and engagement in the CM sessions. As exploratory outcomes, we will explore the effect of CM versus TAU on smoking cessation and abstinence outcomes.

## Methods

### Participants and Eligibility

Inclusion criteria are as follows: (1) veterans enrolled in the San Francisco VA Health Care System (SFVAHCS), (2) those recommended or scheduled for major elective surgery within the next 6 months (eg, general, spinal, thoracic, vascular, urological, gynecological, orthopedic, or other surgeries), (3) those currently (ie, past 30 d) smoking a minimum average of 1 cigarette per day, (4) those having daily access to a personal smartphone device and Wi-Fi, and (5) those open to receiving smoking-cessation interventions. Veterans followed by primary care who are referred to external institutions for major elective surgery will also be eligible.

Exclusion criteria will be evaluated through medical record review and clinical assessment: (1) psychotic, bipolar, or neurocognitive disorders or other psychiatric or medical conditions judged to be unstable in the past 30 days; (2) untreated, current, active problem gambling, as assessed by a medical record diagnosis or a Problem Gambling Severity Index (PGSI) score ≥8; (3) enrollment in end-of-life or palliative care; (4) surgery with a clinical indication for cancer; (5) unable to meet time commitment; (6) currently pregnant or planning to become pregnant during the study [21]; (7) a suicide attempt, or suicidal ideation with intent, within 30 days prior to enrollment; and (8) concurrent participation in another tobacco cessation trial.

### Recruitment and Overall Study Schedule

Participants will be recruited through (1) data queries of VA electronic health record data available through the VA Corporate Data Warehouse and (2) direct recruitment. Data queries will identify patients with an upcoming major elective surgical procedure from a predefined list. We will then identify individuals with documentation of current smoking, using an established approach via the Corporate Data Warehouse national VA database with codes, or “health factors.”

Partners in surgical subspecialties will assist with recruitment through referrals. Direct recruitment will allow the team to recruit participants with a stated interest in tobacco cessation and facilitate targeted recruitment in clinics that serve women and members of underrepresented minority groups. If recruitment rates decrease to below 2 participants per month, we will expand the eligibility criteria from major surgeries to include less invasive eye surgeries and podiatric surgeries.

The protocol eligibility criteria were developed to include participants up to 6 months prior to surgery to improve generalizability after extensive discussions with colleagues in surgery. Surgical colleagues described that some elective major surgeries (eg, some orthopedic, vascular, and neurosurgeries) may not be scheduled for months until successful smoking cessation has occurred, given the risks of cigarette smoking and impaired wound healing with some procedures. Therefore, to be as inclusive as possible to a range of participants awaiting scheduling for elective major surgery, the eligibility criteria include participants who smoke up to 6 months prior to surgery. The preoperative period varies by participant and is being tracked in this pilot study.

Once a veteran participant is recruited, we will follow the study timeline as delineated in Table 1. This schedule of enrollment, interventions, and assessments adheres to the latest SPIRIT (Standard Protocol Items: Recommendations for Interventional Trials) guidelines for reporting (Checklist 1) [35].

**Table 1. T1:** Schedule of enrollment, interventions, and assessments.

	Trial period							
	Enrollment		Postrandomization					Closeout
	Screening and baseline		Intervention phase					Follow-up
Time point (wk)	Week −4	Week 0^a^	Week 1	Week 2	Week 3	Week 4	Week 5	Week 6^a^
Time window (d)^b^	30	7±14	7	7	7	7	7	7+14
Enrollment								
Eligibility screen	✓							
Informed consent	✓							
Medication evaluation		✓				✓		
Randomization		✓						
Postrandomization—intervention or comparator								
Contingency management (CM)								
Treatment as usual (TAU)			✓	✓	✓	✓	✓	
Assessments								
Medical record review	✓	✓						✓
Concomitant medical and mental health treatment	✓	✓						✓
Kessler Psychological Distress Scale	✓							
Columbia-Suicide Severity Rating Scale	✓							
Timeline Followback (TLFB)^c^	✓							✓
Problem Gambling Severity Index	✓							
Urine pregnancy test^d^	✓							
Demographics Questionnaire		✓						
Nicotine and Tobacco Use Survey		✓						✓
Fagerström Nicotine Dependence Questionnaire		✓						✓
Contemplation Ladder—Tobacco Smoking		✓						✓
Questionnaire of Smoking Urges (QSU)^e^		✓						✓
12-Item Short Form Health Index		✓						✓
Exhaled carbon monoxide (CO)								✓
Salivary cotinine^f^								✓

a Week 0 and week 6 can be completed within a 14-day window after the scheduled week. Participants can start week 0 (baseline) earlier, that is, −14 days, if the process is efficient in completing the screening and baseline tasks; or the +14 day window can be used to complete all baseline assessments. At week 6, the typical week 6 range is 7 days, but we allow up to 14 days after week 6 to complete all follow-up measures, if needed.

b Given that the study population includes patients with a high degree of medical complexity and comorbidities, dates are approximate, and assessments can occur on alternate dates if the patient is managing medical appointments that conflict with assessment time points (including but not limited to, chemotherapy, radiation, hospitalization, etc). Alternate scheduling to account for medical comorbidities will occur at the discretion of the principal investigator and co-investigators.

c Cigarette smoking might be reassessed in week 0 to ensure data collected covered past 30 days prior to randomization/intervention phase. Time frames for TLFB in general are past 30-day for screening, past 7-day at weekly session, and days between last TLFB assessment and follow-up assessment for CM condition; and past 30-day for screening and days between the last TLFB assessment and follow-up assessment for TAU condition. TLFB will cover all the days since 30-day prior to screening to the last day of week 6.

d Only individuals aged 18 to 55 years with childbearing potential will be required to take a urine pregnancy test.

e One item from the QSU will be used for assessing craving weekly during CM intervention. This has been specified in Table 2.

f Salivary cotinine will be used as needed to resolve the inconsistency between the CO results. Individuals with CO levels >6 ppm, who report smoking cannabis via TLFB and are not taking any formulation of nicotine, salivary cotinine <10 ng/ml will be used.

**Table 2. T2:** Mobile contingency management (mCM) intervention protocol.

mCM components	Week				
	1	2	3	4	5
iCO Smokerlyzer^a^/iCO app training (daily, weekend, and holidays optional)					
iCO Smokerlyzer/CO video uploads (daily, weekends, and holidays optional)					
CM^b^ incentive (daily)					
Behavioral counseling and clinician feedback session (once weekly)	✓	✓	✓	✓	✓
Assessments^c^					
Timeline Followback (TLFB)	✓	✓	✓	✓	✓
Questionnaire of Smoking Urges (QSU)^d^	✓	✓	✓	✓	✓

a The Smokerlyzer (coVita) is a breath carbon monoxide (CO) device that aids smoking cessation by measuring the amount of CO in the breath of a smoker.

b CM: contingency management.

c Assessments (TLFB and QSU) will be administered weekly to assess past 7-day smoking and the level of craving.

d One item from the QSU will be used for assessing craving weekly.

### Randomization and Blinding

Eligible participants will be randomly assigned to either CM or TAU in a 1:1 ratio, stratified by (1) biological sex and (2) cigarettes per day (≥10 or <10 cigarettes per day) using random permuted blocks via REDCap. We will examine subgroups in exploratory analyses. Due to staffing constraints, no member of the study team will be blinded.

### Measures and Data Collection

#### Demographic, Exclusionary, and Baseline-Only Measures

Demographic characteristics will be collected at baseline. Participants will complete the PGSI [36], a validated 9-item self-report measure of problem gambling behaviors, where a score of ≥8 indicates problem gambling, and Kessler Psychological Distress Scale [37], a validated 10-item survey that measures emotional states, in which a score of 30 and over is likely an indication of severe mental problem. The principal investigator (PI) will assess participants’ past-30-day suicidality via Columbia-Suicide Severity Rating Scale per VA suicide screening procedures [38] and conduct a thorough chart review to confirm mental stability for participating in the study.

#### Outcome Measures

##### Smoking Measures

Smoking cessation outcomes will be administered at baseline and posttreatment. A Nicotine and Tobacco Use Survey (NTUS) developed internally will assess age at first use, duration of use, use of all forms of nicotine and tobacco, prior quit attempts (ie, intentionally not smoking for ≥24 h), duration of cessation (if any), and presence of other tobacco users in the home. Posttreatment assessment will include frequency and duration of quit attempts in the past 30 days. The Fagerström Test for Nicotine Dependence (FTND) [39] is a validated instrument of the severity of physiological addiction to nicotine. The Contemplation Ladder [40] is a validated single-item measure of motivation to quit smoking. The Questionnaire of Smoking Urges [41,42] is a validated 10-item measure that assesses cigarette craving and withdrawal. It will also be administered weekly to assess craving via 1 item, *“*I have a desire for a cigarette right now,” via a scale from 0 (strongly disagree) to 100 (strongly agree) [42]. The Timeline Followback (TLFB) [43,44] is a validated, staff-administered instrument that uses anchor dates to prompt recall of substance use. It will be used to document cigarette, tobacco, electronic nicotine delivery system (ie, e-cigarette), cannabis, any other substance uses, and TUD medications. Participants who are in CM condition will be assessed at screening for past 30-day use, at weekly sessions for past 7-day or days since the last TLFB assessment, and at follow-up visit for days since the last TLFB assessment; participants who are in TAU condition will be assessed at screening for past 30-day use and at follow-up visit for days between the last TLFB assessment and follow-up assessment. Bioverification using mobile CO monitor will also be used to verify abstinence at follow-up visit. If there is inconsistency between self-report and bioverified CO level, a salivary cotinine test might be adopted as needed.

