#### Primary Outcomes: Smoking Cessation

Frequency of quit attempts will be assessed using NTUS and TLFB, defined as a period of intentionally not smoking for ≥24 hours. Number of cigarettes per day will be assessed by TLFB; nicotine dependence severity will be assessed via FTND.

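### Timeline Followback smoking data are collected weekly in the CM arm but in one long recall in the TAU arm; compare cigarettes per day and quit attempts only on windows asked alike in both

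*Protocol article*

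**What the plan says.** The Smoking Measures section sets the TLFB timetable by arm. After a 30-day TLFB at screening, CM participants are asked "at weekly sessions for past 7-day or days since the last TLFB assessment, and at follow-up visit for days since the last TLFB assessment". For TAU the same section provides only the screening TLFB and one at follow-up: "participants who are in TAU condition will be assessed at screening for past 30-day use and at follow-up visit". Table 1, footnote c, repeats the split: the TAU time frames are "past 30-day for screening and days between the last TLFB assessment and follow-up assessment for TAU condition". It adds that smoking may be reassessed at week 0, but does not require it. Table 2, footnote c, confirms the weekly collection in CM: "Assessments (TLFB and QSU) will be administered weekly to assess past 7-day smoking and the level of craving".

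Under Primary Outcomes: Smoking Cessation, "Number of cigarettes per day will be assessed by TLFB", with no averaging window. Quit attempts come from both the NTUS and the TLFB, with no rule on which governs. The Abstract says the arms are compared on these outcomes over 5 weeks, and the Data Analytic Plan models them across time by condition. Smoking Measures, by contrast, says smoking outcomes are administered at baseline and posttreatment.

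The TLFB is staff-administered and, under Randomization and Blinding, "no member of the study team will be blinded".

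On the end of the TLFB, Table 1, footnote c, says "TLFB will cover all the days since 30-day prior to screening to the last day of week 6". The same footnote also runs it to the follow-up assessment, and footnote a lets that assessment fall up to 14 days after week 6.

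**The concern.** A between-arm contrast is interpretable only if both arms are measured in the same way. Here one arm reports recent days in short instalments, and the other reconstructs the whole treatment period in one sitting. If cigarettes per day is averaged over the treatment weeks, or 24-hour abstinent periods are counted from the TLFB over those weeks, recall length is fully tied to arm. A mixed model with condition, time and their interaction cannot separate a recall difference from an effect of CM, and neither multiple imputation nor censoring weights address it. Two of the three smoking outcomes listed as primary (quit attempts and cigarettes per day) draw on the TLFB; dependence severity does not.

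A smaller point concerns the stop date. Read literally, a TLFB that ends on the last day of week 6 would not reach a visit held up to 14 days later.

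**Working it through.** The plan gives no figure for recall length, so there is none to reproduce, and its sample-size figure plays no part here. The spans below follow from Table 1: weeks 1 to 5 are days 1 to 35, week 6 is days 36 to 42, and the extension runs to day 42 + 14 = 56.

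**1. Length of the single TAU recall**
- TLFB redone at the end of week 0, visit at the start of week 6: 35 days (5 weeks).
- The same, visit at the end of week 6: 42 days (6 weeks).
- The same, visit at the end of the extension: 42 + 14 = 56 days (8 weeks).
- No week 0 TLFB, week −4 to week 6 by label: 10 × 7 = 70 days (10 weeks).
- The same with the extension: 70 + 14 = 84 days (12 weeks).

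Summing the full Table 1 windows instead of the labels gives 30 + 7 + 35 + 7 = 79 days, or 93 with the extension, so 12 weeks is not a hard ceiling.

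**2. CM recall over the same period**
- With every session kept, each weekly recall covers 7 days. After a session on day 35, the follow-up recall covers about 1 to 21 days.
- A missed session lengthens CM recall, because the text allows days since the last TLFB.
- With no week 0 TLFB, the first CM session could also reach back from the end of week 1 to week −4, about 5 weeks. Those extra days precede treatment; week 1 itself is still recalled within days.

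**3. Mean lag for treatment days 1 to 35**
- CM, sessions at the end of each week: lags 0 to 6 days, mean 3.
- TAU, visit on day v: mean lag = v − 18. Day 36 gives 18, day 42 gives 24, day 56 gives 38.
- Difference for a day-42 visit: 24 − 3 = 21 days, or 3 weeks.

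**4. What that could do (illustration on assumed figures)**

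Assume a true 10 cigarettes per day in both arms and a reporting error of 1% to 5% per week of lag. Spurious difference = 10 × error × lag difference in weeks.
- Day 42 visit: 10 × 0.01 × 3 = 0.3 to 10 × 0.05 × 3 = 1.5 cigarettes per day.
- Day 36 visit (15 days, 2.14 weeks): about 0.2 to 1.1.
- Day 56 visit (35 days, 5 weeks): 0.5 to 2.5.

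The sign reverses if longer recall over-reports instead of under-reporting. The documents give no error rate.

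**5. Measures that escape the problem**
- Last 7 days before the visit, asked at the visit: lags 1 to 7 days, mean 4, in both arms.
- Screening TLFB: 30 days in both arms.
- NTUS quit attempts: past 30 days at posttreatment, with no distinction by arm.

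**6. How much of treatment the NTUS item covers**

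The window is days v − 30 to v − 1.
- Day 36: days 6 to 35, so 30 of 35 treatment days.
- Day 42: days 12 to 41, so 24 of 35.
- Day 56: days 26 to 55, so 10 of 35.

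CM's recommended quit date is in week 2 (days 8 to 14), so a late visit can miss an attempt made then.

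**The case against.** The strongest reply is that nothing obliges the analyst to set weekly CM data against the single TAU recall. Smoking Measures speaks of baseline and posttreatment, and a short posttreatment window has equal lag in both arms. The averaging window may be fixed in a full protocol or analysis plan that is not shown. This stands in part: the problem is conditional on the window. But the Abstract's comparison over 5 weeks and the across-time model point to the treatment weeks, and the unequal collection is stated in the text, not inferred from silence.

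A reader might infer that every TLFB comparison is biased. The documents do not support that. Seven-day abstinence is defined identically in both arms and checked by CO, the screening TLFB is the same in both, and the NTUS offers a quit-attempt measure asked alike in both.

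A reader might also infer that the 7 days of self-report and the CO test would not adjoin. That rests on one phrase. Smoking Measures and the preceding sentence of footnote c run the TLFB to the follow-up assessment, and footnote a treats the extension as part of completing week 6. It is loose wording to be reconciled, not a demonstrated gap.

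Finally, the TLFB is described as validated and uses anchor dates to prompt recall, and the efficacy comparison is exploratory and deliberately unpowered. Both points limit the weight of the concern. They do not make the two procedures alike.

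**Conclusion.** The concern holds in a limited form. TLFB timing differs by arm, so cigarettes per day averaged over the treatment weeks and TLFB-derived quit attempts would be measured differently in CM and TAU, by unblinded staff. The contrast in mean lag is about 3 against 24 days for a day-42 visit (18 to 38 days in TAU across the permitted visit window), assuming all CM sessions are kept.

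This is a risk of differential measurement error, not a demonstrated bias: the documents establish neither its size nor its direction. A reader might take the primary-outcome heading over these measures to make this a must-fix. However, the Study Objectives and the Power Analysis treat efficacy as exploratory and unpowered in a 36-person pilot, and an arm-neutral measure is available for each affected outcome. It is a cheap improvement to an exploratory comparison.

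**What to change.** - **Cigarettes per day:** compare the arms on the mean over the 7 days before the week 6 visit, against the same 7-day measure at baseline. Ask those 7 days at the visit in both arms, because when the visit falls early in week 6 some of them will already have been reported at the CM week 5 session.
- **Quit attempts:** base the between-arm comparison on the NTUS past-30-day item. Re-asking CM participants about the whole period would be weaker, since they have already rehearsed it weekly while TAU would be recalling it for the first time.
- **Weekly CM TLFB:** use it only descriptively within CM.
- **Table 1, footnote c:** reconcile its statements so that the TLFB runs to the actual follow-up visit.

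The cost is mainly analysis wording. TLFB data are recorded by day and the NTUS item is already scheduled, so most of this can also be applied to the 18 participants enrolled by May 2026. The downsides are that the finer weekly CM data stay out of the between-arm test, and that the 30-day NTUS window does not cover the whole 5 weeks, less so the later the visit.
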